## Abstract

**Background:**

The UK has one of the highest fatality rates for deaths from fire-related injuries in children aged 0–14 years; these injuries have the steepest social gradient of all injuries in the UK. Children’s centres provide children under five years old and their families with a range of services and information, including home safety, but their effectiveness in promoting injury prevention has yet to be evaluated. We developed a fire prevention intervention for use in children’s centres comprising an Injury Prevention Briefing (IPB) which provides evidence on what works and best practice from those running injury prevention programmes, and a facilitation package to support implementation of the IPB. This protocol describes the design and methods of a trial evaluating the effectiveness and cost-effectiveness of the IPB and facilitation package in promoting fire prevention.

**Methods/Design:**

Pragmatic, multicentre cluster randomised controlled trial, with a nested qualitative study, in four study centres in England. Children’s centres in the most disadvantaged areas will be eligible to participate and will be randomised to one of three treatment arms comprising: IPB with facilitation package; IPB with no facilitation package; usual care (control). The primary outcome measure will be the proportion of families who have a fire escape plan at follow-up. Eleven children’s centres per arm are required to detect an absolute difference in the percentage of families with a fire escape plan of 20% in either of the two intervention arms compared with the control arm, with 80% power and a 5% significance level (2-sided), an intraclass correlation coefficient of 0.05 and assuming outcomes are assessed on 20 families per children’s centre. Secondary outcomes include the assessment of the cost-effectiveness of the intervention, other fire safety behaviours and factors associated with degree of implementation of the IPB.

**Discussion:**

This will be the first trial to develop and evaluate a fire prevention intervention for use in children’s centres in the UK. Its findings will be generalisable to children’s centres in the most disadvantaged areas of the UK and may also be generalisable to similar interventions to prevent other types of injury.

**Trial registration:**

http://NCT01452191 (date of registration: 13/10/2011).

## Background

Globally, injuries are an important cause of morbidity and mortality in childhood [1]. The UK does not compare well with other high-income countries, having one of the highest rates for deaths from fire and flames in children aged 0–14 years [2]. In 2011–12, the English Fire and Rescue Service attended 44,300 house fires with 21 fatalities in those under 16 years with 35 times that number injured [3].

Within countries there are steep social gradients in childhood fire-related deaths and injuries, which disproportionately affect the disadvantaged [4]. In England and Wales, children whose parents had never worked or were long-term unemployed have death rates from exposure to smoke, fire and flames 38 times higher than those of children whose parents had managerial/professional occupations [5].

There is evidence that some interventions are effective in reducing the risk of fire-related injuries and in promoting fire prevention practices. Smoke alarms reduce risk of death in house fires [6,7]. Education, with or without safety equipment being provided, is effective in increasing the prevalence of functioning smoke alarms [8,9] and home safety education increases the prevalence of fire escape planning [8]. Despite this, there is little evidence of the systematic implementation of such injury prevention in the NHS [10] and it is unlikely that this is any different in the social care or the voluntary sectors. A recent systematic review identified the main barriers and facilitators to implementing injury prevention interventions; these included the type of approach used (one-one; group work; partnership working; tailored methods), characteristics of the deliverer, the complexity of the intervention, accessibility to safety equipment and the importance of achieving behavioural change [11]. It is therefore important that interventions to promote injury prevention take these barriers and facilitators into account.

Children’s centres provide community-based integrated services, information and support for families with pre-school children. They aim to improve outcomes for young children and their families, with a particular focus on the most disadvantaged, in order to reduce inequalities in health [12,13]. Home safety is within the remit of children’s centres consequently they have the potential to promote fire prevention and to reach a population at particular risk of fire-related injury. We have therefore developed a fire prevention intervention for use in children’s centres, comprising an Injury Prevention Briefing (IPB) which provides evidence on what works and best practice from those running injury prevention programmes and a facilitation package to support implementation of the IPB. The five key messages in the intervention are: the importance of smoke alarm use and maintenance, having a family fire escape plan, identifying potential causes of house fires, safe storage of matches and lighters and having a bedtime fire safety routine. This protocol describes a trial evaluating the effectiveness and cost-effectiveness of the IPB and facilitation package in promoting fire prevention.

### Objective

The objective of the trial is to evaluate the effectiveness and cost effectiveness of an educationally based intervention (IPB) with or without facilitation, as a means of changing behaviours to improve fire safety in the home.

## Methods/Design

A three-arm multicentre cluster randomised controlled trial, with an economic analysis and a nested qualitative study, set in 4 trial sites in England (Nottingham, Bristol, Norwich and Newcastle). We chose a cluster randomised controlled trial because the intervention will be delivered at the level of children’s centres and to prevent contamination between treatment arms that could have arisen through individual treatment arm allocation of families living in close proximity.

### Participants

#### Children’s centres

Children’s centres were established in phases, with the first phase being those in the most disadvantaged areas. Children’s centres in the four trial sites will be eligible to participate if their catchment area has more than 50% of under-5 year-old children living in one of the 30% most disadvantaged Super Output Areas in England [14]. Children’s centres will be invited to take part by post followed by a telephone call and a face-to-face visit at which a consent form will be completed by the children’s centre manager and baseline data will be obtained. Priority will be given to phase one children’s centres who will be invited to participate first, and invitations will be extended to phase two children’s centres if the sample size requirements are not fulfilled with phase one centres.

### Families

Families who have attended the participating children’s centre in the previous three months, who have a child under three years old and who live within the catchment area of that children’s centre will be eligible to participate. Families where a parent is under 16 years of age will be excluded from participation.

Families will be recruited using a range of strategies including:

1. Trial information is sent by post;

2. Children’s centre staff approach families face-to-face either in the centre or in the family home and provide information;

3. Children’s centre staff introduce families to a member of the research team who explains the trial and provides trial information.

Those agreeing to take part will complete a consent form and baseline questionnaire, either at the children’s centre or at home and return them by post. Participants will only be considered to be recruited to the trial if they complete a consent form and the baseline questionnaire.

### Intervention

The intervention will comprise an IPB, bringing together information from the scientific literature on effectiveness and best practice in fire prevention from people who run injury prevention programmes in the field and a package to facilitate its implementation. The intervention was developed using the UK Medical Research Council (MRC) guidance for the development and evaluation of complex interventions [15] and included the following stages:

1. Identifying the evidence base.

Evidence about the effectiveness of interventions was ascertained from systematic reviews of interventions to prevent injuries from house fires [8,9,16]; facilitators and barriers for home injury prevention interventions for pre-school children [11] and decision-analyses related to the prevention of house fires [17].

Evidence about the design, content and delivery of the intervention came from several sources. These included the Health Development Agency [18] 'Effective Action Briefing’ for putting evidence into practice for the promotion of domestic smoke alarms [19] and a review of the literature on the implementation and facilitation of health promotion interventions undertaken as preliminary work for this trial. This identified one framework which we used to guide the design and evaluation of the facilitation package: the PARIHS framework (Promoting Action on Research in Health Services) [20] and Carroll’s fidelity framework [21] which we used to measure the fidelity of the intervention. The PARIHS framework provides three interacting core elements of evidence, context and facilitation and the Carroll framework informs measurement of fidelity in terms of adherence to an intervention; exposure or dose; quality of delivery; participant responsiveness and programme differentiation.

2. Identifying appropriate theory.

We developed our intervention based on factors thought to explain most health-related behaviours across five behavioural change theories comprising the health belief model, social cognitive theory, the theory of reasoned action, the theory of self-regulation and self-control and the theory of subjective culture and interpersonal relations, as described in the review of behaviour change theories for injury prevention by Gielen and Sleet [22]. Three factors were described as necessary and sufficient for producing a behaviour:

a. The person forms a strong positive intention or makes a commitment to perform the behaviour;

b. There are no environmental barriers that make it impossible to perform the behaviour;

c. The person possesses the skills necessary to perform the behaviour.

Our intervention therefore aimed to help individual participants (both children’s centre staff and families) form intentions to change behaviour, remove environmental barriers and to provide participants with the skills to perform the behaviour.

3. Modelling processes and outcomes.

We interviewed national and local leaders who had responsibility for policy and operational matters related to children’s centres. We undertook four workshops, one in each trial site, with local practitioners and policy makers, including children’s centre managers and staff, the Fire and Rescue Service, NHS staff and commissioners of children’s services. These were designed to allow input from potential end-users and those with specialist expertise in implementation to the design of the IPB and facilitation package. They were also used to ensure the IPB complemented and recognised existing fire prevention initiatives, built on existing knowledge about how to implement programmes in children’s centres and how to reach families in the community. We used postal surveys [23], interviews with children’s centre managers and staff and structured interviews with parents attending children’s centres [24] to develop an understanding of current injury prevention activities, including parents’ understanding and use of fire escape plans. We also used interviews with parents of pre-school children to explore barriers and facilitators to injury prevention.

### Allocation to intervention and delivery of intervention

Once the required number of families have been recruited at a children’s centre, the children’s centre will be randomised to one of three arms: IPB plus facilitation, IPB only or usual care (control arm) (see below for method of randomisation). The intervention will be delivered over 12 months.

Children’s centres in the IPB plus facilitation arm will be given the following:

a) The fire prevention IPB containing (i), information for children’s centre managers on why preventing fire-related injuries is important, who the target group is, what interventions can be provided, creative ways of reaching the target group and how to evaluate their use of the IPB and (ii), information for children’s centre staff on why preventing fire-related injuries is important, who is at greatest risk, what are the main causes of house fires, what staff can do to help, what works to prevent house fires, where to get specialist advice and help and examples of activities they can do with parents, including session plans and resources covering smoke alarms, fire escape plans, the causes of house fires, children’s development and behaviour and risk of house fires and bedtime safety routines. Children’s centres will be asked to deliver the fire prevention messages to families participating in the trial over a twelve month period, using whatever format they think is most appropriate for their families. If they are unable to deliver all messages, they are asked to focus on smoke alarms and fire escape plans as these are the most evidence based.

b) A training session will be provided by the Child Accident Prevention Trust and the research team focussed on the IPB and its potential use within a children’s centre setting. This comprises an introduction to children’s injuries in general and fire-related injuries in particular; the development, principles and content of the IPB, opportunities to practice using the IPB and to develop an outline plan for how the IPB might be implemented and a discussion of data collection requirements for the trial.

*Facilitation contacts* at month 1, 3 and 8 will use a two-stage approach comprising a postal or electronic questionnaire followed by a face-to-face or telephone interview, depending on progress with implementing the IPB. A fourth contact will be made at months 4 to 5 if there is no progress with implementation of the IPB at month 3. The facilitation contacts will collect information on the progress of IPB implementation, staff engagement, consistency of delivery, address questions and discuss barriers to implementation, give advice and examples of good practice from other centres and provide a resource list, contact with other organisations and address other questions or concerns. To maximise potential usability of the intervention after the trial, the facilitation package was designed to be similar to the advice and support that might be provided by an injury prevention coordinator (as recommended in NICE guidance on injury prevention [25]).

IPB only arm: the IPB will be posted to children’s centres and no training or facilitation will be provided.

Control arm: children’s centres will continue to provide their usual information on home safety. The IPB will be posted to children’s centres after collection of post-intervention data.

### Outcome measures

#### Definition of primary and secondary outcome measures

The primary outcome will be the proportion of families who report that they have a fire escape plan at 12 months follow-up.

Secondary outcome measures will include:

### Family participants

1. The proportion of families with a high level of fire escape planning behaviour (using a binary measure of fire escape plan behaviour derived from five component items using latent variable analysis. The component items are: having door keys accessible, having window lock keys accessible, having a torch beside the bed, knowing the sound of a smoke alarm and having exits clear.);

2. The proportion of families with smoke alarms fitted and working on every level of their home;

3. The proportion of families who report fire setting or match play by their children;

4. A bedtime fire safety routine score;

5. The proportion of families who have accessed smoking cessation services;

6. Number of correct responses to fire safety knowledge questions;

7. The proportion of families who were fairly satisfied or very satisfied with home safety information provided by children’s centres;

8. Implementation of the IPB assessed by:

a. The proportion of families who received advice on each of the 5 key messages in the IPB in the last year;

b. The proportion of families who attended a fire safety session in the last year;

c. The number of fire safety sessions attended by families in the last year;

d. The proportion of families who attended a fire safety session at a children’s centre in the last year;

e. The proportion of families who attended sessions about each of the 5 key messages in the IPB in the last year;

9. Families’ resource-use and expenditure in relation to fire safety practices.

### Children’s centres as participants

10. The proportion of children’s centres providing information and advice on fire prevention;

11. Resource-use and expenditure incurred in relation to fire safety practices in all three arms;

12. Reported implementation of the IPB within children’s centres;

13. The identification of barriers and facilitators to children’s centres implementing the IPB.

All outcome measures will be ascertained at 12 months follow-up, defined as 12 months post commencement of the intervention in the IPB plus facilitation and IPB only arms and 12 months post randomisation in the control arm.

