### Ascertainment of outcomes

Outcomes measured at the level of families and children’s centres will be ascertained using a range of tools delivered as summarised in Table 1 and described below.

**Table 1 T1:** Tools for measuring parent and children’s centre outcomes by treatment arm

**Data collection tool**	**IPB plus facilitation arm**	**IPB only arm**	**Control arm**
*Data collected from families*			
Baseline self-completion questionnaire	x	x	x
Post-intervention self-completion questionnaire	x	x	x
*Data collected from children’s centres*			
Baseline manager/staff questionnaire	x	x	x
Post-intervention manager/staff questionnaire	x	x	x
Facilitation contacts questionnaire at 1, 3, 4/5 and 8 months	x	x	
Facilitation contacts interview at 1, 3, 4/5 and 8 months	x	x	
Activity logs	x	x	x
Post-intervention facilitation questionnaire	x	x	
Post-intervention facilitation interview	x	x	
Post-intervention implementation fidelity questionnaire	x	x	
Post-intervention implementation fidelity interview	x	x	

*Note*: post intervention is 12 months post commencement of the intervention in the IPB plus facilitation and IPB only arms and at 12 months post randomisation in the control arm.

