### Ascertaining children’s centre outcomes

Information will be collected from children’s centres managers or staff on the promotion of fire prevention using a postal questionnaire at baseline and post intervention in the IPB plus facilitation arm and the IPB only arm, and at baseline and 12 months post randomisation in the control arm. Questions will be based on those used in a national survey of injury prevention activity amongst children’s centres in England [28]. Questions concerning resource use related to implementing the IPB will be included in the post-intervention questionnaire for all arms of the trial. The baseline questionnaire was piloted on 10 children’s centres across England who were not selected to take part in the trial and minor modifications were made.

During the intervention period, data on process measures such as the number of fire prevention sessions provided by the children’s centre, number of centres with a written plan for implementing the IPB, number of staff trained in delivering the IPB per centre, number of specific fire safety sessions from the IPB provided for parents and number and type of other methods used by each centre to reach parents with fire safety messages (e.g. home visits by outreach workers, incorporation of fire safety messages in existing activities) will be ascertained from the IPB plus facilitation arm through the facilitation contacts questionnaire and interviews and the activity logs.

Post-intervention, information on the implementation of the IPB will be ascertained from an implementation fidelity questionnaire and from implementation fidelity interviews, with centre managers and/or staff responsible for the delivery of the IPB in the IPB plus facilitation and the IPB only arms of the trial. The questionnaire and interview schedule will be based on the Carroll framework [21], on the review of the literature on the implementation and facilitation of health promotion interventions undertaken for the trial, the systematic review of barriers and facilitators to home injury prevention [11] and findings from interviews of children’s centre managers and staff described above. Data collected from the range of outcome measurement tools will be mapped onto the PARIHS framework [20] (described above) to explore the success of the implementation process.

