### Randomisation

Once 30 families have been recruited at a children’s centre, centres will be stratified by trial site (4 strata: Nottingham, Bristol, Norwich, Newcastle) and randomly allocated within strata to one of three arms using permuted block randomisation, with a block size of 3. The allocation schedule will be produced by an independent statistician, using the randomisation algorithm in Stata. These lists will be provided to an independent administrator who will prepare sequentially numbered opaque envelopes (one set for each of the four trial coordinating centres) with these allocations.

Children’s centres will be randomised in trios, once each stratum contains 3 children’s centres. In this way, allocation will be concealed from the children’s centres and the researchers up to the point of actually randomising a trio of centres. Once a stratum contains 3 children’s centres, the administrator will open the envelopes for each block of 3 children’s centres, record the allocations and notify each of the trial coordinating centres of the allocation. Children’s centres will then be notified of their allocation by email.

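### The 12-month follow-up runs from start of intervention in the two IPB arms but from randomisation in control, so any lag makes the measurement time depend on arm

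*Protocol article*

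**What the plan says.** The primary outcome has a single nominal time point: "The primary outcome will be the proportion of families who report that they have a fire escape plan at 12 months follow-up". Under Children's centres as participants the article defines that time point. The definition covers everything ("All outcome measures will be ascertained at 12 months follow-up") and differs by arm: "12 months post commencement of the intervention in the IPB plus facilitation and IPB only arms and 12 months post randomisation in the control" arm.

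The rule is not a slip. The note to Table 1 repeats it ("post intervention is 12 months post commencement of the intervention in the IPB plus facilitation and IPB only arms and at 12 months post randomisation"). Ascertaining children's centre outcomes uses the same anchors for the centre questionnaires, post intervention in the IPB arms "and at baseline and 12 months post randomisation in the control arm".

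Four other parts of the article bear on it:

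- **Families.** Consent and the baseline questionnaire are needed before a family counts as recruited, and a centre is randomised only after its families are recruited. Baseline therefore precedes randomisation in every arm.
- **Randomisation.** Centres "will be randomised in trios, once each stratum contains 3", so the three centres of a block share a randomisation date.
- **Allocation to intervention and delivery of intervention.** The facilitated arm has a training session, and the IPB-only arm is sent the document by post. Delivery is planned to last 12 months.
- **Primary outcome measure.** The model adjusts for site, three centre-level variables, baseline fire escape plan and deprivation score. It lists no term for follow-up time.

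**The concern.** Randomising a trio together gives three comparable centres at one moment. The follow-up rule keeps that moment as time zero for the control centre and replaces it with a later, arm-specific event for the other two. If training or posting takes place some time after randomisation, IPB families are asked about their fire escape plan later than control families of the same trio. They have had longer since baseline and are in a different calendar period, possibly another season or a different phase of local fire-safety activity. Their children are slightly older.

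None of this is caused by the IPB, yet all of it is aligned with arm. Any background change in fire escape planning over the extra interval would be counted as intervention effect, or would mask it. The same applies to every secondary outcome. Because training must be arranged and a posting need not be, the lag may also differ between the two active arms.

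**Working it through.** **1. Measurement times side by side.** Let L be the time from randomisation to start of intervention.

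| Arm | Time from randomisation to outcome | Step before delivery |
|---|---|---|
| IPB plus facilitation | 12 months + L₁ | training session |
| IPB only | 12 months + L₂ | posting |
| Control | 12 months | none |

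The arms match only if L₁ = L₂ = 0. The article does not say this and gives no upper limit for L. A shared randomisation date within a trio does not help, because the follow-up date is not tied to it in two of the three arms.

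**2. The plan's own sample size, as a reference scale.** Inputs from Sample size: 42% in control, a 20-point difference (so 62%), two-sided 5%, 80% power, ICC 0.05, 20 families per centre, 33% loss.

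- Two proportions with continuity correction: 107 families per arm.
- Design effect: 1 + (20 − 1) × 0.05 = 1.95.
- Centres per arm: 107 × 1.95 / 20 = 10.43, rounded up to 11, as stated.
- Families per centre: 20 / (1 − 0.33) = 29.9, rounded up to 30; 36 × 30 = 1080, as stated.

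The sample size reproduces and is not affected by this point.

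**3. Illustration of the bias (assumed lag and trend).** Suppose there is no intervention effect, fire escape planning drifts linearly by D points a year in all arms, and L is the same in both IPB arms.

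- Bias = D × L / 12.
- Effective size per arm with 12 centres of 20 families: 240 / 1.95 = 123.1.
- Standard error of a difference at 42%: √(2 × 0.42 × 0.58 / 123.1) = 0.063, or 6.3 points.
- Two-sided error rate = 1 − Φ(1.96 − bias/SE) + Φ(−1.96 − bias/SE), with the SE computed at the two shifted proportions.

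| Assumed drift per year | Lag | Bias (points) | Error rate |
|---|---|---|---|
| 5 points | 1 month | 0.4 | 0.051 |
| 5 points | 3 months | 1.25 | 0.055 |
| 5 points | 6 months | 2.5 | 0.068 |
| 10 points | 1 month | 0.8 | 0.052 |
| 10 points | 3 months | 2.5 | 0.068 |
| 10 points | 6 months | 5.0 | 0.124 |

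For example, 5 × 3 / 12 = 1.25 points, about a fifth of the 6.3-point standard error. An upward drift favours the IPB arms and a downward drift works against them.

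**The case against.** The rule has a purpose. Delivery is planned for 12 months, and anchoring at the start of intervention gives both IPB arms that full period. Several implementation outcomes ask families about the preceding year, and the current anchor lines that recall window up with delivery. Both points stand. They do not require the control arm to run on a different clock: a common trio date set at the planned training or posting date largely preserves both.

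The effect may also be small. A lag of a few weeks, or even 3 months with a 5-point annual drift, barely moves the error rate. This stands and limits the severity.

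A journal article may leave the definition of commencement and its scheduling limits to the full protocol. That absence is not the complaint here. The complaint is the arm-dependent anchor, which the article does state.

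Three stronger readings are tempting, and the article does not support them:

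- **A centre that never starts has no follow-up date, which breaks intention-to-treat.** The facilitation schedule provides an extra contact at months 4 to 5 for centres with no implementation progress by month 3. The month count therefore appears to run before delivery has progressed, which suggests that it starts at training or posting, events in the trial team's hands. On that reading a non-delivering centre still has a 12-month date.
- **Differential attrition is built in.** Spreading the 33% loss as a constant monthly hazard, −ln(0.67)/12 = 0.0334, would give retention of 64.8%, 62.7% and 60.6% at 13, 14 and 15 months against 67% at 12. But the 33% is a planning allowance, not a rate. Part of such loss is non-response to a questionnaire at one time point, which need not grow with the interval. The lags are assumed too.
- **The difference is beyond the reach of analysis.** With randomisation and questionnaire dates recorded, the interval can be reported by arm and examined in a sensitivity analysis. That is weaker than preventing the difference, but it is not nothing.

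**Conclusion.** The point holds at moderate severity. The article states three times, consistently, that follow-up is timed from different events in the IPB and control arms. Whenever there is a lag, the interval from baseline and randomisation is systematically longer in the IPB arms, for the primary and all other outcomes, and the listed model does not account for it.

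Neither the size nor the direction of any bias can be derived, because the article gives no lag and no background trend. Under the assumed linear drift it is probably small against the 20-point target if the lag is weeks. It is not negligible if the lag is many months: 5 points at 6 months with a 10-point annual drift. If training and posting coincided with randomisation the problem would vanish, but the article does not say that they do. The case for acting is that the arm-dependence is avoidable at almost no cost, not that a large bias has been shown.

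**What to change.** Use one clock per trio.

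- When a trio is randomised, fix a single start date for all three centres, namely the planned date of training and IPB posting.
- Send follow-up questionnaires to families and centres in all three arms, control included, 12 months after that date, whatever the progress of delivery.
- Amend the definition under Children's centres as participants, the Table 1 note and Ascertaining children's centre outcomes to match.
- Record and report the time from randomisation to questionnaire completion by arm.

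The cost is wording and mailing schedule; the sample size does not change. Control centres wait slightly longer for their IPB. A centre that starts after the common date has slightly under 12 months of delivery when it is measured, and its preceding-year questions then cover a short time before delivery began. Setting the date at planned training or posting keeps both effects small.
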